### Assessment measures

2.3.

The study will involve assessment tools used for the diagnosis and classification of the severity of ASD, with the measurement of cognitive and behavioral aspects, an assessment tool for gross and fine motor skills (primary outcome), a functional mobility test, a test for the assessment of spatiotemporal gait variables, a functional balance scale, a neurophysiological assessment of motor cortical excitability (evoked motor potential) and a questionnaire addressing side effects. In addition, informations about the medications will be collected, including the name of the medication, dosage and frequency of use, and how long the child has been using the medication. The order of evaluations will be random, through simple randomization carried out by draw.

#### Assessment tools and categorization of groups according to ASD

2.3.1.

The Autism Diagnostic Observation Schedule (ADOS) will be used to confirm the diagnosis of ASD and to assess the behavior of the children in terms of particular structured activities. The ADOS is composed of four modules, all with good reliability, sensitivity and specificity for ASD (64, 65). Each module is designed for individuals with specific degrees of linguistic development and involves a protocol of structured, dynamic interactive activities conducted by a trained examiner in a period of approximately 45 min. The aim of the different tasks is to provide information on social behavior, communication and general aspects of the individual being assessed. Based on observations on how the individual performs the tasks, the therapist answers a questionnaire, attributing scores for the different behaviors. The questions are organized on a four-point scale, with 0 indicating no abnormality and 3 indicating moderate to severe abnormalities (66). To be classified as an individual with autism or ASD according to the ADOS, the sum of the scores defined in the algorithms of the four modules must reach minimum cutoff points in the domains referring to communication and reciprocal social interaction (67, 68). The ADOS is an ASD diagnostic instrument, but we also chose to use it in post-intervention assessments, with the intention of identifying possible changes in the participants’ performance during the execution of tasks.

The Brazilian version of the Childhood Autism Rating Scale (CARS-BR) will be administered to the parents or guardians for the classification of the severity of ASD. CARS-BR is an observation scale with 15 items to assist in the identification of children with ASD and distinguish children with impaired development without autism as well as distinguish autistic children with intellectual disability. Its importance consists of the differentiation of mild to moderate autism from severe autism. The scale is short and appropriate for use on any child older than two years of age. The scale was validated for Brazilian Portuguese in a study conducted for 15 years involving 1,500 children with autism (62). The scale assessed behavior in 14 domains generally affected by autism plus a general autism impression category. The scores of each domain range from 1 (within the limits of normality) to 4 (severe autistic symptoms). The overall score ranges from 0 (no characteristics of autism) to 60 (all severe characteristics met). Its use offers several advantages over other instruments, such as the inclusion of items that represent varied diagnostic criteria and reflect the actual dimension of the disorder, applicability to children of all ages (including preschoolers) and objective, quantifiable scores based on direct observation (62).

#### Neurofunctional assessment measures

2.3.2.

##### Primary outcome

2.3.2.1.

Gross and fine motor skills: Motor skills will be assessed using the Movement Assessment Battery for Children-2 (MABC-2). The principal aim for the use of this measure will be the assessment of balance using a valid measure for children with ASD (69, 70) employed in a previous clinical trial analyzing the effects of tDCS in this population (59). The MABC-2 comprises the categories of manual dexterity, aiming and catching and balance, with norms of the tests for three different age groups (3–6 years, 7–11 years and 12–17 years). The balance subscale has three items for each age group (one static and two dynamic tests). The standard score based on age is equivalent in percentile for each subscale to be transcribed from the raw score of the child. The percentiles are normally used to guide the interpretation when explaining the scores obtained on the test to parents and teachers, with the following zones: (a) Red zone – scores equal to or lower than the 5th percentile; (b) Amber zone – scores between the 5th and 15th percentile; and (c) Green zone – scores above the 15th percentile (69–71).

The MABC is used to identify motor difficulties in children and is particularly associated with the identification of Developmental Coordination Disorder (DCD). The assessment has been used and validated with several atypical populations, including those with ASD. Since there is no recommendation or guideline for evaluation of motor ability in individuals with ASD, the MABC was an optimal choice for the present study. Several studies have shown that individuals with ASD have motor difficulties consistent with DCD. In Miller et al. (72), over 90% of the cases in the ASD group met criteria for co-occurring DCD. In a recent systematic review, the majority of articles (92.5%) indicated that 50–88% of children with ASD had significant motor impairments on standardized motor assessments and/or functional questionnaires. The nature of motor and function problems in ASD were consistent with DCD (6).

##### Secondary outcomes

2.3.2.2.

Functional balance: The Pediatric Balance Scale will be used for the assessment of functional balance. This scale is composed of 14 items that address the performance of functional balance common to daily living. Each item is scored on a five-point scale ranging from 0 to 4, with a maximum total score of 56 points. The points are based on the time in which a position is maintained, the distance to which an upper limb is capable of reaching in front of the body and the time required to complete the task. The children will perform the tasks barefoot. The average duration of test is 30 min (73, 74).

Functional mobility: The Timed Up and Go (TUG) test (75) will be performed with the aid of the inertial G-sensor (BTS Bioengineering), which is widely used for the assessment of functional mobility. The TUG test consists of the time in seconds required for the individual to stand up from a standard chair without using the arms, walking three meters, turning around, returning to the chair and sitting down again. The children will be instructed to perform the test safely at a self-selected pace. The test will be performed three times – the first two for familiarization and the third will be used for analysis. The variables obtained during the execution of the TUG test with the use of the G-sensor and analyzed in the study will be the duration of the phases and peak of the trunk in angular space: duration of the task (s), duration of the phase from sitting to standing (s), going gait (s), duration of turning phase (s), return gait (s), duration of final turning phase (s), duration of phase from standing to sitting (s), duration sitting to standing – peak trunk flexion (°), duration of sitting to standing – peak trunk extension (°), duration standing to sitting – peak trunk flexion (°), duration of standing to sitting – peak trunk extension (°). The average duration of the TUG test is 120 s.

Spatiotemporal gait variables: Spatiotemporal gait variables will be determined during the execution of the Walk Test (76). The participants will be instructed to remain standing and, when instructed, walk normally without running for ten meters, turn around a cone, return, turn around and return to the initial position. During the execution of the test, spatiotemporal gait variables will be collected by the inertial sensor (G-Sensor®, BTS Bioengineering S.p.A. Italy), enabling gait analysis with the Walk Test. The portable G-sensor is a wireless system of inertial sensors for human movement analysis. The sensors are controlled by a data recording unit (up to 16 elements) using ZigBee radio communication. Each sensor is 62 mm × 36 mm x 16 mm, weighs 60 g and is composed of a three-axis accelerometer (maximum scale: ± 6 g), a three-axis gyroscope (complete scale: ± 300°/s) and a three-axis magnetometer (complete scale: ± 6 Gauss). Only one sensor will be used in the study, with data collected at a sampling frequency of 50 Hz. The data from the inertial sensor will be transmitted *via* Bluetooth to a computer and processed using the BTS G-STUDIO, version 2.6.12.0, which automatically furnishes the variables. The participants will perform the test three times – two for familiarization and the third for analysis. The following variables will be collected: duration of the gait cycle (s), cadence (steps/min), velocity (m/s), stride length (m) of left and right lower limbs and step length (%) of left and right lower limbs. The procedure will last an average of 10 min.

#### Neurophysiological assessment measure

2.3.3.

Cortical excitability: Transcranial magnetic stimulation (TMS) will be used for the assessment of cortical excitability using a magnetic stimulator with a circular MagVenture coil. The response to stimulation applied to the motor cortex will be recorded in the thumb adductor and femoral quadriceps of both limbs to identify the motor evoked potential (MEP) and the motor cortical representation pattern (contralateral, bilateral or unilateral). The MEP responses will be filtered and amplified using a surface electromyograph. The signals will be transferred to a personal computer for offline analysis using data collection software. The motor threshold and MEP will be measured using the single-pulse TMS method. The motor threshold will be found in the region of the cortex with the lowest intensity necessary to generate a peripheral response. The same method will be employed to determine the MEP using 110% of the motor threshold intensity. Ten measures of the MEP will be performed in each assessment step.

#### Adverse effects assessment measure

2.3.4.

Potential adverse effects of tDCS will be investigated after each intervention using a questionnaire administered to the child. The children will be asked about the perception of any of the following symptoms during the session: tingling sensation, burning sensation, headache, pain at the sites where the electrodes were positioned, sleepiness and change of mood. The children will be instructed to answer using a three-point scale: 1 – “I did not feel it at any time during the session”; 2 – “I felt it at some times during the session”; 3 – “I felt it during the entire session.” When a child reports an adverse effect (answers 2 or 3), she or he will be asked to quantify the intensity (0 – none, 1 – weak, 2 – moderate, 3 – strong or 4 – unbearable). The children will be asked openly prior to each session about the occurrence of headache, pain on the scalp, burning sensation, tingling, redness of the skin, sleepiness, concentration difficulty or mood swings during periods between sessions. Considering the potential for impaired communication, the guardians will also be asked about their perceptions and the therapists in charge of the intervention will be instructed to observe and report behaviors suggestive of discomfort. The questionnaire has a maximum duration of 5 min for its application.

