### Intervention procedures

2.4.

The ten intervention sessions will be held over 2 consecutive weeks, with five sessions per week (Monday to Friday). Upon arrival to the session, the participants and guardians will be oriented and prepared to undergo the intervention. The electrodes will be positioned and the child will perform 20 min of neurofunctional training combined with tDCS. At the end of each session, the child will answer the questionnaire on adverse effects. Neurofunctional training associated with tDCS will be performed by two investigators. One investigator will be responsible for conducting the neurofunctional training and the other for the tDCS, ensuring that the electrodes remain properly positioned during the neurofunctional training. In addition, the tDCS equipment used indicates the quality of contact between the electrodes and the cranial surface and the maintenance of current flow, indicating the intensity applied throughout the intervention period. Therefore, even minimal changes can be easily identified.

Transcranial direct current stimulation: Transcranial stimulation will be administered using the tDCS device (Soterix Medical Inc., USA) with two sponge (non-metallic) surface electrodes (5 × 7 cm2) moistened with saline solution. The children will be randomly allocated to three types of treatment: 1) anodal tDCS over the primary motor cortex; 2) anodal tDCS over the cerebellum; and 3) sham tDCS. Following the 10–20 International Electroencephalogram System (77), the group to receive anodal tDCS over the primary motor cortex will have the anode positioned over Cz and the cathode positioned over the right deltoid muscle, whereas the group to receive anodal tDCS over the cerebellum will have the anode positioned one centimeter below the inion and the cathode positioned over the central supraorbital region (47). For sham stimulation, all electrode placement procedures will be performed using the montage over the primary motor cortex.

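### The between-session adverse-effect enquiry names scalp pain as its local-pain item, so delayed pain at the shoulder electrode used in the motor-cortex and sham arms is not a named item

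*Protocol article*

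**What the plan says.** Section 2.3.4 (Adverse effects assessment measure) sets out two enquiries with different symptom lists.

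- **After each session**, about what was felt during it: tingling, burning, headache, "pain at the sites where the electrodes were positioned, sleepiness and change of mood". Positive answers are graded for intensity.
- **Before each session**, about the interval since the last one: "The children will be asked openly prior to each session about the occurrence of headache, pain on the scalp, burning sensation, tingling, redness of the" (the quote stops at skin redness). The list then goes on to "sleepiness, concentration difficulty or mood swings during periods between sessions".

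Because some children may communicate poorly, the section adds that "the guardians will also be asked about their perceptions", and that the treating therapists are to report behaviour that points to discomfort.

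Section 2.4 (Intervention procedures) fixes the electrode sites. The motor-cortex arm has the "anode positioned over Cz and the cathode positioned over the right deltoid muscle". The cerebellar arm has the anode 1 cm below the inion and the cathode in the midline above the orbits. For the control arm: "For sham stimulation, all electrode placement procedures will be performed using the montage over the primary motor cortex".

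**The concern.** The two lists in Section 2.3.4 ask about local pain in different terms. The post-session item follows the electrodes wherever they are. The pre-session item is tied to one body region, and in two of the three arms one electrode is outside that region. A child with a sore shoulder on the day after a session would not be prompted for it by name.

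Two things are at stake. The first is completeness: the post-session questionnaire is confined to the session itself, so the pre-session enquiry is the one described for delayed symptoms. The participants are three to eight years old and need only follow simple verbal commands (Section 2.2), so a symptom that is not named is less likely to be volunteered. The second is comparability: if the item suits one montage better than another, a table of between-session pain by arm partly reflects how the question was worded. The Discussion hopes that the trial will help in choosing the target area for stimulation, and tolerability by montage bears on that choice.

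**Working it through.** No arithmetic applies: the plan gives no rate of delayed local pain and no figure to reproduce. The check sets the symptom lists of Section 2.3.4 against the electrode sites of Section 2.4, arm by arm.

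| Arm | Anode | Cathode | Post-session pain item (during session) | Pre-session pain item (between sessions) |
|---|---|---|---|---|
| Motor cortex | Cz | right deltoid | both sites | Cz covered; deltoid not named |
| Sham | Cz | right deltoid | both sites | Cz covered; deltoid not named |
| Cerebellum | 1 cm below inion | central supraorbital | both sites | both on the head; covered only if scalp (or headache) is read to include forehead and sub-inion area |

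What follows, step by step:

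1. **During sessions** there is no gap. The item refers to the electrode sites, so both sites are covered in every arm.
2. **Between sessions** the only named pain items are headache and scalp pain. Neither describes pain over the deltoid. One of two electrode sites is therefore not named in the motor-cortex and sham arms, that is, in two of three arms.
3. **Other between-session items.** Burning, tingling and skin redness carry no site limit, so they would be picked up at the shoulder as well as on the head. They are not pain, but they overlap with it.
4. **Motor cortex versus sham.** Same electrode sites, same question: ascertainment is equal. Equal wording guards against an artificial difference, but it does not recover shoulder pain that is missed in both arms.
5. **Cerebellum versus either other arm.** Ascertainment of delayed local pain may differ. Whether it does depends on how scalp is read for the two cerebellar sites, and the article calls neither of them scalp. On the broad reading the cerebellar arm is fully covered and the others are not. On the strict reading the cerebellar arm also has sites that the item does not name.

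**The case against.** The strongest reply is that the practical gap is small and that the same section already provides for it. The enquiry is open, three of its local-symptom items have no site limit, and guardians and therapists are added as reporters precisely because the children may not speak up. Adverse effects are neither the primary nor a listed secondary outcome, and Section 2.5 describes no between-arm test of harms. The article also condenses a form that is not shown.

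Most of this stands, and it limits the point to a minor one. It does not remove it. The guardian enquiry is stated without any prompt about the shoulder. Therapists see the child at sessions, not in between. Burning and redness are not pain. And this is not something left to a fuller document: the article states the item, and the item does not fit the montages that the article also states.

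Stronger readings are tempting and should be resisted:

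- A reader might infer that **only scalp pain is asked about**. That is not so: headache and the site-free sensory and skin items are in the same sentence.
- A reader might infer that **local pain is covered at both electrodes only in the cerebellar arm**. That is untrue of the post-session questionnaire, and for the between-session enquiry it rests on a broad reading of scalp.
- A reader might infer **a bias towards more recorded pain in the cerebellar arm**, or try to put a percentage on the pain that is missed. The first needs that same broad reading. The second needs an assumed split of pain between the electrodes and the assumption that every other route of reporting catches nothing. The documents support neither.

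**Conclusion.** The point holds in a limited form. The between-session enquiry uses a local-pain item that does not match the electrode placement in the motor-cortex and sham arms, whereas the post-session item does. Delayed pain at the deltoid site may therefore be under-recorded in those arms, and between-session local pain may be recorded unequally between the cerebellar arm and the other two. The contrast of motor cortex with sham is not affected by unequal ascertainment.

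Neither the size nor the direction of any effect can be established. No rate of delayed pain is given, it could be zero, and the reading of scalp for the forehead and sub-inion sites is open. The conclusion assumes that the form in use follows the wording of the article. Severity is minor: it concerns the completeness and consistency of safety data and touches no efficacy analysis.

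**What to change.** In the pre-session enquiry of Section 2.3.4, replace the scalp-pain item with the one that the section already uses after each session: "pain at the sites where the electrodes were positioned". Put it in the same words to child and guardian in all three arms. The two lists then agree on local pain, and the item no longer depends on the montage.

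The cost is one reworded item on an existing form, with no extra visit, staff or procedure and no change to the intervention. If children have already been assessed with the scalp wording, record the date of the change and say in the report which between-session data were collected under which item.

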### Intervention procedures

2.4.

The ten intervention sessions will be held over 2 consecutive weeks, with five sessions per week (Monday to Friday). Upon arrival to the session, the participants and guardians will be oriented and prepared to undergo the intervention. The electrodes will be positioned and the child will perform 20 min of neurofunctional training combined with tDCS. At the end of each session, the child will answer the questionnaire on adverse effects. Neurofunctional training associated with tDCS will be performed by two investigators. One investigator will be responsible for conducting the neurofunctional training and the other for the tDCS, ensuring that the electrodes remain properly positioned during the neurofunctional training. In addition, the tDCS equipment used indicates the quality of contact between the electrodes and the cranial surface and the maintenance of current flow, indicating the intensity applied throughout the intervention period. Therefore, even minimal changes can be easily identified.

Transcranial direct current stimulation: Transcranial stimulation will be administered using the tDCS device (Soterix Medical Inc., USA) with two sponge (non-metallic) surface electrodes (5 × 7 cm2) moistened with saline solution. The children will be randomly allocated to three types of treatment: 1) anodal tDCS over the primary motor cortex; 2) anodal tDCS over the cerebellum; and 3) sham tDCS. Following the 10–20 International Electroencephalogram System (77), the group to receive anodal tDCS over the primary motor cortex will have the anode positioned over Cz and the cathode positioned over the right deltoid muscle, whereas the group to receive anodal tDCS over the cerebellum will have the anode positioned one centimeter below the inion and the cathode positioned over the central supraorbital region (47). For sham stimulation, all electrode placement procedures will be performed using the montage over the primary motor cortex.

The participants in the active tDCS groups will receive an electrical current at an intensity of 1 mA during the 20 min of neurofunctional training. The intensity of the current will be gradually increased in the initial 30 s, remain at 1 mA for 20 min and gradually reduced in the final 30 s. For the sham intervention, the current will be gradually increased to 1 mA in the initial 30 s, giving the children the initial sensation of the electrical current, but no stimulation will be administered for the rest of the session. This is considered a valid control procedure in studies involving tDCS (30).

Neurofunctional training: The training was carried out in a therapy room organized specifically for the intervention. Composed of postural control training and gait training. Immediately after the onset of tDCS (active or sham), the three groups will perform neurofunctional training consisting of postural control exercises and treadmill training conducted by a trained, experienced physiotherapist, with the participants performing the intervention individually. The 20 min of intervention will be divided into two steps (10 min each).Treadmill training: The training was performed on a Inbramed treadmill (Milenium ATL model, RS, Brazil). The treadmill training speed will be established based on the performance of the child in each session. Ideal speed will be the maximum speed at which the child is able to walk with adequate support of the feet upon initial contact and throughout the entire support phase of the gait cycle. The speed will be gradually increased during the initial two minutes and gradually reduced during the final two minutes, maintaining a constant speed in the interim. During training, the children used their habitual shoes, which were duly placed by the physiotherapist. The therapist remained behind the participants, facilitating gait training if necessary and ensuring both the safety of the intervention and the best possible movement kinematics. Throughout treadmill training, the therapist in charge also provided verbal commands to the participant to improve the execution of gait (48, 78).Postural control exercises: The second step will involve a circuit of activities based on the tasks of the MABC-2 to favor the improvement in postural control. The activities will be four exercises performed for 40 s with a 20-s rest interval. The four exercises will be selected individually according to the performance of each child during the MABC-2. Items from the balance and aim subscale will be defined as circuit exercises, which the child is able to perform with a delay (does not reach the complete performance of the item) and with qualitative observations in aspects of posture/body control. Some examples of activities are: balancing on one foot, walking on tiptoes, jumping, etc. During the execution of the circuit activities, the physiotherapist will remain beside the child, guaranteeing his/her safety in the face of imbalance and offering verbal commands with motivational phrases and guidance for the steps of the activities. Each participant will perform two complete circuits, with a two-minute rest interval between circuits.

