### General study design

2.1.

A randomized, sham-controlled, double-blind study will be conducted involving children with a diagnosis of ASD. We will compare three montages: anodal tDCS over the primary motor cortex, anodal tDCS over the cerebellar region and sham stimulation. Stimulation will be administered in all three groups during 20 min of motor training focused on gait and balance training (Figure 1).

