Withdrawal criteria: Participants who decline to continue in the study, those not present on the days of the experiment and those who miss up to two of the 10 intervention sessions will be removed from the study.

**Randomization procedure:** Randomization will be performed using a program for the generation of random numbers to allocate the participants to one of the following interventions:Experimental group 1 – Motor cortex stimulation: anodal tDCS over the primary motor cortex combined with neurofunctional motor training;Experimental group 2 – Cerebellar stimulation: anodal tDCS over the cerebellar region combined with neurofunctional motor training;Control group – Sham stimulation: sham tDCS combined with neurofunctional motor training.

Randomization will be performed considering stratification based on the severity of ASD according to the Brazilian version of the Childhood Autism Rating Scale (CARS-BR) (63). The randomization sequence will be generated for each category (mild, moderate and severe) with adequately organized distribution in sequentially numbered opaque envelopes.

**Blinding:** After the inclusion of participants based on the eligibility criteria and after the pre-intervention assessment, the allocation of the participants will be informed to the researcher who will carry out the intervention. The researcher in charge of the randomization process will not participate in any other aspect of the study and will not have access to the participants. The researchers involved in the assessment procedures, the participants and their families will not be aware of the allocation of the participants. This information will be provided to the families and participants after the complete conclusion of the procedures of the study. The investigator in charge of the interventions will not be blinded to the allocation of the participants, as it will be necessary to select the active or sham stimulation option of the equipment.

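### Sham uses only the motor-cortex electrode placement, so participant and family blinding is not secured for cerebellum versus sham

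*Protocol article*

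**What the plan says.** Section 2.1 labels the trial: "A randomized, sham-controlled, double-blind study will be conducted involving children with a diagnosis of ASD". The blinding paragraph in section 2.2 names who is masked: "The researchers involved in the assessment procedures, the participants and their families will not be aware of the allocation of the participants". The same paragraph says that the investigator delivering the intervention is not masked, because that person has to choose active or sham on the device.

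Section 2.4 describes two placements. The motor-cortex group "will have the anode positioned over Cz and the cathode positioned over the right deltoid muscle". The cerebellar group "will have the anode positioned one centimeter below the inion and the cathode positioned over the central supraorbital region". The sham rule is: "For sham stimulation, all electrode placement procedures will be performed using the montage over the primary motor cortex". Sham current is ramped up in the same way as active current, "but no stimulation will be administered for the rest of the session".

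Section 2.4 also splits the session between two people: "One investigator will be responsible for conducting the neurofunctional training and the other for the tDCS".

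The outcomes most open to family influence appear in three places. Section 2.3.1 has the CARS-BR given to parents or guardians. The Discussion says that ADOS and CARS reflect how relatives see the child. The last paragraph of the Introduction expects motor-cortex effects to be confined to motor outcomes, with cognitive and behavioural effects in the cerebellar arm.

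**The concern.** A sham masks a contrast only if the sham children could be mistaken for the active children. Here a sham child and a motor-cortex child look alike, while a cerebellar child looks like no sham child. The initial ramp imitates the sensation of current. It cannot imitate an electrode on the forehead and another below the inion. The article describes no cerebellar sham, no fitting of both placements on every child and no concealment of the electrodes.

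At stake is the reading of the cerebellar results on family-informed outcomes. If guardians can work out that their child is on active current, a CARS or ADOS advantage over sham cannot be cleanly separated from expectation. The comparison of motor cortex with cerebellum on those outcomes is also uneven: both arms are active, but only one can be recognised as active. The Discussion wants to use that comparison to inform the choice of target area.

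**Working it through.** **Inputs.** Section 2.2 gives a minimum of 24 children (eight per group), 20% dropout and 30 recruited. The inflation reproduces: 24 / (1 − 0.20) = 30. The article does not state the allocation ratio for the 30; 30 / 3 = 10 per group is an assumption, in line with eight per group. The placements are those in section 2.4.

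**Probability of active current given the visible placement, current design.**

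- Cerebellar: active / (active + sham) = 10 / (10 + 0) = 1.00
- Motor cortex: 10 / (10 + 10) = 0.50

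The 1.00 does not depend on group size, because no sham child has this placement. The 0.50 holds for any equal allocation (with eight per group, 8/16).

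**If s of the 10 sham children wore the cerebellar placement.** The probabilities become 10 / (10 + s) for cerebellar and 10 / (20 − s) for motor cortex.

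| s | Cerebellar | Motor cortex |
|---|---|---|
| 0 (current) | 1.00 | 0.50 |
| 2 | 10/12 = 0.83 | 10/18 = 0.56 |
| 5 | 10/15 = 0.67 | 10/15 = 0.67 |

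With s = 5 the placement no longer carries information about active versus sham. Smaller s, as after a mid-trial change, helps only in part.

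**Should placement then be a covariate?** With s = 5 there are four cells: motor cortex active (10), cerebellum active (10), sham with motor-cortex placement (5) and sham with cerebellar placement (5). Three arms plus a two-level placement term use four parameters, so the model is saturated and each adjusted contrast falls back on its own half of the sham arm. Variances in units of σ²:

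- Cerebellum versus pooled sham: 1/10 + 1/10 = 0.20
- Cerebellum versus sham, adjusted for placement: 1/10 + 1/5 = 0.30; standard error ratio √(0.30/0.20) = 1.22, about 22% larger
- Motor cortex versus cerebellum, unadjusted: 1/10 + 1/10 = 0.20
- The same, adjusted: 1/10 + 1/5 + 1/10 + 1/5 = 0.60

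The covariate would undo the pooling, so it does not belong in the primary analysis.

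**The case against.** The strongest reply is that the problem reaches less far than the placement rule suggests.

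- **Deducible is not the same as known.** A person must see the electrodes and also know that sham uses only one placement. The consent material is not shown, so what families are told cannot be checked, and the children are aged three to eight. This stands as a limit. Blinding is not secured; it is not shown to be lost in every family.
- **The primary outcome has its own protection.** The MABC-2 is a performance test. Section 2.2 says assessors are unaware of allocation, and section 2.1 places assessments at separate visits one, four and eight weeks after treatment. Nothing puts assessors in the sessions, and the statistician is blinded (section 2.5). This stands: assessor blinding can survive if families do not disclose what they saw.
- **Coaching.** A reader might infer that the physiotherapist's encouragement biases only the cerebellar contrast. That requires a trainer who is otherwise blind, which the article does not state. If the trainer falls under the unblinding declared in section 2.2, coaching could affect both active-versus-sham contrasts.
- **The behavioural measures are not purely family reports.** ADOS is scored by a trained examiner, CARS-BR is also described as observation-based, and both are secondary. Section 2.9 expects cognitive and behavioural gains without limiting them to one arm. This reduces the exposure but does not remove it, given what the Discussion says about family perceptions and what the Introduction predicts for the cerebellar arm.

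**Conclusion.** The concern holds in a limited form. The statements in sections 2.1 and 2.2 that the trial is double-blind and that participants and families are unaware of allocation are not secured for cerebellum versus sham, because the cerebellar placement always means active current (10/10, against 10/20 for the motor-cortex placement, assuming 10 per group). They can hold for motor cortex versus sham.

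The main exposure is CARS and ADOS in the cerebellar arm, and motor cortex versus cerebellum on those outcomes. The document gives no basis for putting a size on the bias.

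A reader might go further and call the whole cerebellum-versus-sham comparison unblinded, including the MABC-2. The article does not support that, since it states that assessors are blind and schedules assessment away from the sessions.

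**What to change.** 1. **Sham placement.** For children not yet randomised, allocate sham children about equally to the two electrode placements. Balance this over the whole sham arm: with about 10 sham children across three severity strata, exact halves within each stratum are not feasible.
2. **Analysis.** Keep sham as one pooled arm in the primary analysis, without a placement covariate. Give the placement-matched contrasts as a sensitivity analysis only.
3. **Who is unblinded.** Reconcile sections 2.2 and 2.4: only the tDCS operator, who selects active or sham, should be unblinded, and the training physiotherapist should be kept unaware of the setting. This works in the cerebellar arm only with step 1, because otherwise the placement reveals the setting.
4. **If too late.** Section 2.8 has recruitment running from January to December 2023. If too many children are already treated, restrict the double-blind claim: state that cerebellum versus sham is assessor-blind but not reliably participant- or family-blind, and interpret CARS and ADOS in that arm accordingly.

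**Cost.** A protocol amendment and a revised randomisation list, with no extra children, staff or devices. The sham arm becomes slightly heterogeneous, with about five children per placement if done from the start. A mid-trial change leaves earlier sham children as they are and partly confounds sham placement with calendar time. The stimulation site itself remains visible; what is restored is the masking of active versus sham. Step 4 alone costs only a change of wording.
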